**1. [Research subject name]**

A prospective randomized controlled trial to investigate the effect of yokukansan on perioperative anxiety and pain

**3. [Purpose and significance of research]**

It is known that excessive perioperative anxiety causes an increase in blood pressure and tachycardia. On the other hand, reducing excessive perioperative anxiety is known to be shortened the postoperative course and hospitalization period and postoperative pain. Benzodiazepine anxiolytics have traditionally been used as pre-anesthetic medications to reduce perioperative anxiety [1], but benzodiazepines can cause excessive sedation, and their use tends to be withheld [2]. Moreover, severe postoperative pain can be a risk factor for postoperative chronic pain due to the delay in motor function recovery that inhibits rehabilitation [3]. Anticonvulsants such as pregabalin and various anxiolytics for perioperative anxiety have been tried as measures against postoperative pain, but there are problems such as ineffectiveness and strong side effects.

Yokukansan is a type of Chinese herbal medicine that has been used for night crying, and hysteria in children but recently is used for dementia-associated symptoms [4] and neuropathic pain [5]. Yokukansan is thought to have a reducing effect on excitability and some effect on pain and emotions. The applicant has also been prescribing yokukansan for patients with neuropathic pain or increased pain due to anxiety at an outpatient clinic. A study examining the effects of yokukansan on perioperative anxiety and sedation levels [6] suggests that yokukansan has the effect of suppressing anxiety while minimizing sedation. No clinical studies have been conducted to investigate whether or not it is effective for postoperative pain. We planned this study because we thought that the anxiolytic and analgesic effects of yokukansan might also benefit perioperative patients.

[1] J. K. Carroll E, et al, *British Journal of Nursing*. 2012; 21(8):479-483

[2] P.F. White, B. et al, *Anesthesia and Analgesia*. 2009; 108(4)1140-1145

[3] Patricia R. Pinto, et al, Journal of pain research. 2012;13(11)1045-1057

[4] Matsunaga S, et al, J Altzheimers Dis. 2016;54(2) 635-43

[5] Nakamura Y, et al, Masui. 2009; 58(10) 1248-55

[6] Young-Chang Arai, et al, Evidence based Complementaly and Alternative Medicine.2014; ID965045

**4. [Research method and period]**

① Research implementation period

From November 1, 2017 to March 31, 2021.

② Information on drugs used

Name: Tsumura Yokukansan (Product number: 054)

Route of administration, dosage and administration: Oral, 1 packet (2.5 g) at a time

Dosage form: Extract granules

③ Research subjects

Patients aged 20 to 60 years who undergo breast cancer surgery at Niigata University Medical and Dental Hospital or Niigata Prefectural Cancer Center Niigata Hospital and undergo total mastectomy and sentinel lymph node biopsy, or partial mastectomy and sentinel lymph node biopsy (Details will be described later).

④ Research method

Multicenter / Open Label / Superiority test by forced random sampling

[1] A pre-treatment questionnaire survey will be conducted on all subjects, and the age, BMI, surgical history, and general status (American Society of Anesthesiologists-Physical Status: ASA-PS, ECOG-PS) will be recorded in advance. Also, before taking the study drug, record the measurement of amylase in saliva, the Hospital anxiety and depression scale (HADS), and the State Trait Anxiety Inventory (STAI).

[2] Subjects are assigned to two groups, one with yokukansan (intervention) and the other without (control), according to the results of randomization. The intervention group should be given 1 packet (2.5 g) of TSUMURA Yokukansan before sleep on the day before surgery and 1 packet (2.5 g) 2 hours before entering the operating room on the day of surgery. For the purpose of maintaining the same quality between the two groups, a forced allocation algorithm is created, and if a bias is confirmed between the groups, forced allocation is performed based on age, surgical history, etc.

[3] Subjects in the intervention group take 1 packet of yokukansan orally 2 hours before entering the operating room on the day of surgery, and then all participants are measured salivary amylase in the operating room. Anesthetized by general anesthesia in the operating room and undergo total or partial mastectomy and sentinel lymph node biopsy

[4] Record salivary amylase measurements, HADS, STAI, visual analog scale of pain: VAS, QOR (Quality of recovery), and the presence or absence of analgesic use 24 hours after surgery.

| 24-hour before surgery | Salivary amylase  HADS STAI |
| --- | --- |
| Just before surgery | Salivary amylase |
| 24-hour after surgery | Salivary amylase  HADS STAI  Visual analog scale for postoperative pain  QOR  Rescue analgesics usage |

※The allowable range is ± 12 hours before and 24 hours after surgery.

⑤ Sample size

In this study, we plan to perform Bayesian analysis. In this method, the posterior probability of the response rate is calculated by an interim analysis, and the calculated posterior probability is monitored. If it is judged that the effect is not as good as that of untreated, the test should be discontinued. Is planned. In addition, since the posterior predictive distribution is obtained based on the data obtained from the interim analysis, it is possible to judge whether the additional data follows the distribution, and it is possible to save the number of cases by performing this procedure. Is known to be. As an interim analysis, an exploratory analysis will be performed when 20 cases in a group are reached based on reference [1]. Recalculate the required number of cases based on the results of the interim analysis. Regarding the design of the number of cases, referring to the previous study, 1-β was 80%, the significance level was 0.05, and the success rate of the intervention group (yokukansan was expected to be taken preoperatively and preoperatively: impression at the outpatient clinic of pain clinic) is set to 75%. About 40 cases are expected in each group. The clinically meaningful difference is defined as σ = 0.3.

[1]Young-Chang Arai, et al, Evidence based Complementaly and Alternative Medicine.2014; ID965045

⑥ Study endpoints

Primary endpoint: Salivary amylase level

Secondary endpoint: HADS STAI QOR Pain VAS

⑦ Analysis method

Statistical analysis methods are planned to be performed by the maximum likelihood estimation method and the Bayesian statistical method. All analysis is performed by a person in charge of analysis different from that of the principal investigator.

For maximum likelihood estimation methods, t-tests that do not correspond to continuous variables, Fisher's exact test for scale classification, and Mann-Whitney U test for continuous variables or ordinal variables that do not follow a normal distribution such as VAS. A test will be used to determine P <0.05 as significant.

For Bayesian statistics, the difference between two independent groups is estimated for the primary endpoint. A pre-analysis will be conducted based on the uniform distribution obtained in the exploratory test and the data of 20 subjects, and the obtained distribution will be used as the prior distribution to generate and verify the posterior distribution using the data of 40 subjects in each group.

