**8. [Handling of personal information, etc.]**

All persons in charge of this study shall comply with the "Declaration of Helsinki (revised in October 2013)" and the Clinical Research Law. When publishing the results of the study, do not include information that can identify the subject. In addition, we will not use the materials of the subjects obtained in the research other than the purpose of the research.

**9. [Burden on research subjects and expected risks and benefits, comprehensive evaluation of these, and measures to minimize the burden and risks]**

Patients in the control group of this study do not take any medication and therefore do not suffer any benefit or disadvantage. On the other hand, patients in the intervention group have the disadvantages of having to take the drug even if it is difficult to take it, and the side effects of Chinese herbs may occur.

The side effects of yokukansan have been reported to be hypokalemia, gastrointestinal disorders (diarrhea and nausea), liver dysfunction, etc., but the frequency is stated to be less than 0.1-5% in the package insert. All of them are side effects of long-term continuous use (reported in 13 days at the earliest). Most of them occur in the elderly aged 65 and over. Since this time, the drug was taken only twice, it is highly unlikely that such side effects will occur. In the unlikely event that yokukansan causes health problems, the researcher will deal with it in good faith and provide appropriate medical care. The cost will be covered by the subject's insurance, and no special compensation will be provided by this study. The collection period for adverse events should be continuous from the acquisition of consent to the end of the study.

**10. [Procedures for collecting, recording, and reporting information on diseases, etc. (including identification of important diseases, etc. that the principal investigator should report to the principal investigator and abnormal values ​​of clinical tests, and requirements and deadlines for reporting) and outbreaks of diseases, etc. Observation period of subjects for later clinical studies]**

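### The unqualified open label does not keep the anaesthetist or the 24-hour outcome collector unaware of the arm, and premedication and intraoperative analgesia are not recorded.

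*Protocol*

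**What the plan says.** All references are to the Protocol.

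- **Masking.** Section 4, ④ Research method, gives the design as "Multicenter / Open Label / Superiority test by forced random sampling". It does not say who is or is not told the allocation. Section 9 states: "Patients in the control group of this study do not take any medication". There is no placebo.
- **Dosing.** The first packet is taken before sleep on the evening before surgery. For the second: "Subjects in the intervention group take 1 packet of yokukansan orally 2 hours before entering the operating room on the day of surgery".
- **Anaesthesia.** Section 4 ④ [3] says only: "Anesthetized by general anesthesia in the operating room and undergo total or partial mastectomy and sentinel lymph node biopsy". It describes neither premedication nor intraoperative analgesia.
- **Recorded items.** Section 4 ④ [4] lists the postoperative assessment: "Record salivary amylase measurements, HADS, STAI, visual analog scale of pain: VAS, QOR (Quality of recovery), and the presence or absence of analgesic use 24" (the closing figure is in hours). The only co-treatment on the schedule is whether rescue analgesics were used.
- **Endpoints.** Section 4 ⑥: "Primary endpoint: Salivary amylase level", with no time point named, and "Secondary endpoint: HADS STAI QOR Pain VAS".
- **Separation of roles.** Section 4 ⑦: "All analysis is performed by a person in charge of analysis different from that of the principal investigator". The analyst is not said to be blinded.

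**The concern.** With an untreated control, open label is unavoidable for the patient and for whoever hands over the packet. It is not unavoidable for the anaesthetist or the person who collects the 24-hour outcomes, yet the plan does nothing to keep them unaware.

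Two things could follow. An anaesthetist who knows that a patient had no study drug might give more analgesia, which would pull the arms together. A collector who expects benefit might, when administering a scale or prompting an answer, pull them apart. The trial data as scheduled would not show the first, because premedication and intraoperative analgesia are not among the items collected.

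Expectation of benefit is on record. Section 3 says the applicant already prescribes the drug for neuropathic pain and for pain heightened by anxiety, and section 4 ⑤ bases the assumed 75% success rate on an impression from the pain clinic. The study is run from anaesthesiology (sections 12 and 14), and it covers two hospitals whose habits may differ.

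**Working it through.** **Step 1: who needs the allocation, and when.**

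| Event | Timing | Is the arm needed for the trial task? |
| --- | --- | --- |
| First packet | Evening before surgery | Yes, by whoever supplies it |
| Second packet | 2 hours before operating-room entry | Yes, by whoever supplies it |
| Operating-room amylase | Just before surgery | No |
| General anaesthesia and surgery | After that sample | No |
| Amylase, HADS, STAI, VAS, QOR, rescue use | 24 hours after surgery | No |

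The last three rows all follow the last dose. No trial task in them depends on the arm.

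**Step 2: which outcomes are exposed.**

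- *Pain VAS, QOR, HADS and STAI* are all taken at 24 hours, after any arm-aware choice of analgesia, and by a collector who may know the arm.
- *24-hour amylase* comes after anaesthesia and analgesia and could respond to them. It matters for the primary endpoint only if this is the time point meant, and section 4 ⑥ does not say.
- *Operating-room amylase* comes before anaesthesia in section 4 ④ [3] and is listed in the schedule as just before surgery. Intraoperative choices cannot reach it; premedication could. Exclusions ⑥ to ⑧ in section 5 (2) are worded for drugs a patient is already taking or has already taken, so they do not clearly bar premedication given later. No document says that any is given.

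**Step 3: how large a shift would matter.** The documents give no figure for this bias, so the calculation is illustrative.

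Inputs: 40 per group (section 4 ⑤); significance level 0.05 (section 4 ⑤), taken as two-sided; pain VAS SD 20 mm (assumed); no true effect; systematic shift *b* between arms (assumed); normal approximation.

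- SE = SD × √(2/n) = 20 × √(2/40) = 20 × 0.2236 = 4.47 mm
- P(reject) = [1 − Φ(1.96 − b/SE)] + Φ(−1.96 − b/SE)
- b = 2.5 mm: b/SE = 0.559; P = 0.0806 + 0.0059 = 0.086, or 8.6%
- b = 5 mm: b/SE = 1.118; P = 0.1999 + 0.0010 = 0.201, or 20.1%

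In SD units no SD need be assumed, since b/SE = (shift in SD) ÷ 0.2236:

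| Shift (SD) | False-positive rate |
| --- | --- |
| 0 | 5.0% |
| 0.1 | 7.3% |
| 0.2 | 14.5% |
| 0.3 | 26.9% |
| 0.5 | 60.9% |

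A shift of the same size in the other direction would hide that much of a true effect. Section 4 ⑦ assigns VAS to the Mann-Whitney U test, so these normal-theory rates are approximate.

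**The case against.** The strongest reply has five parts.

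1. *The label does not say that staff are told.* A reader might infer that the anaesthesia team and collectors do know the arm. The Protocol applies the label to the trial and is silent on roles. This stands: the point is that an unqualified label permits it and nothing prevents it.
2. *The primary endpoint is a measurement.* A reader might infer that assessor expectation biases the operating-room amylase. The documents show no route by which the person taking saliva would change the value, and the sample precedes anaesthesia. This stands. The only remaining route is premedication, and that is speculative: section 3 remarks that benzodiazepines tend to be withheld, and no sedative is described in either arm.
3. *Patients know their arm.* HADS, STAI, VAS and QOR rest on the patient's own report, so masking staff leaves patient expectation in place. This stands and limits the gain. The scales may also already be self-completed; the Protocol does not say.
4. *The information is not lost.* A reader might infer that unequal co-treatment could never be disentangled. Co-treatments would ordinarily be in the anaesthesia and ward records, and section 11 keeps source material available for inspection. The gap is in what the trial plans to collect, and it can be closed by extraction.
5. *Staff may overlap.* The trial is run from anaesthesiology, and section 10 sends complication reports to anaesthesia doctors at each hospital. Those who enrol or allocate may also anaesthetise or collect. This stands as a limit on feasibility.

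What survives is that two roles could be kept unaware where staffing allows, and that co-treatment should be recorded.

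**Conclusion.** The point holds as a design weakness that is cheap to reduce. It is neither a contradiction nor an arithmetic error. Who is masked during conduct belongs in the Protocol, and naming an analyst other than the principal investigator does not protect data already generated.

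The exposure falls on all four secondary endpoints and on the primary only if 24-hour amylase is meant. The direction cannot be predicted: compensating analgesia for controls would mask an effect, and hopeful collection would create one. The illustrative false-positive rates run from 7.3% at a 0.1 SD shift to 26.9% at 0.3 SD (60.9% at 0.5 SD). They rest on assumed shifts and on 40 per group; the millimetre figures also rest on the assumed SD. They show that modest shifts matter at this sample size, not that such shifts will occur.

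**What to change.** Add to section 4 ④:

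- Where feasible with existing staff, the treating anaesthetist and the 24-hour outcome collector are not told the allocation, which stays available for safety. Where a hospital cannot separate these roles, it says so.
- Patients complete HADS, STAI, QOR and the pain VAS themselves.
- Premedication and intraoperative and postoperative analgesic use are copied from the anaesthesia and ward records in both arms, and reported by arm and hospital.
- Patients know their arm, so expectation bias in the self-reported scales remains and will be acknowledged when results are interpreted.

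None of this sets or changes any clinical regimen.

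*Cost:* some Protocol wording, a few extra data fields, and care to keep the allocation off routine operating-room handover. Masking will be partial because patients can disclose their arm. Recording co-treatment is useful even where masking fails, since an imbalance would then be visible.

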**5. [Policies for selecting research subjects]**

(1) Research subjects

① Patients aged 20 to 60 years who have been diagnosed with breast cancer and undergo total mastectomy and sentinel lymph node biopsy, or partial mastectomy and sentinel lymph node biopsy at Niigata University Medical and Dental Hospital or Niigata Prefectural Cancer Center Niigata Hospital

② Patients who received written and oral explanations regarding this study and showed their consent to participate in writing.

(2) Exclusion criteria

① Patients with preoperative condition classification (ASA-PS) 4 or higher by the American Society of Anesthesia

② Patients with BMI (Body Mass Index ≥ 30)

③ Patients who already have pain that requires oral painkillers somewhere in the body except for the primary disease

④ Those who are allergic to the drug used

⑤ Persons with hypokalemia

⑥ Patients taking anti-anxiety drugs and antipsychotic drugs

⑦ Patients who are already taking painkillers including opioids

⑧ Patients who have already taken some Chinese medicine

⑨ Patients who have difficulty communicating (dementia, mental retardation, mental illness, do not understand Japanese, etc.)

⑩ Other patients who are judged to be inappropriate by the principal investigator and the investigator

(3) Cancellation criteria

① When the research subject offers to decline participation in the research or withdraws consent

② When the entire research is canceled

③ When the result of intraoperative sentinel lymph node biopsy is positive and axillary lymph node dissection is performed

④ When the person in charge of research determines that it is appropriate to discontinue the research for other reasons.

(4) Voluntary research cooperation and freedom of withdrawal

Participation in the study is decided by the patient's free will, and it is possible to withdraw participation at any time. If the patient withdraws from the study before the start of oral administration, it will be excluded from this study. Patients who refuse to take the second dose after the first dose and withdraw from the study are also excluded from this study. Explain that withdrawal of research participation does not result in any disadvantage in subsequent treatment.

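### Randomisation gives way to forced allocation once a group imbalance is confirmed, with no stated trigger, closed factor list, random element or concealed release, in an open-label trial

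*Protocol*

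**What the plan says.** Protocol section 4 ④ describes the design as "Multicenter / Open Label / Superiority test by forced random sampling". Item [2] there gives the basic rule: "Subjects are assigned to two groups, one with yokukansan (intervention) and the other without (control), according to the results of randomization". To keep the arms comparable it then adds that "a forced allocation algorithm is created" and that "if a bias is confirmed between the groups, forced allocation is performed based on age, surgical history, etc".

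Item [1] of the same section says that "the age, BMI, surgical history, and general status (American Society of Anesthesiologists-Physical Status: ASA-PS, ECOG-PS) will be recorded in advance", so the two named balancing factors are known before treatment.

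The protocol does not define a confirmed bias, and does not say who looks for one or when. The factor list is left open. No random element in the forced step is mentioned, and nothing is said about central assignment or concealment.

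**The concern.** Balancing on covariates during recruitment is sound when the rule is fixed in advance, applies from the first patient, keeps an element of chance and is concealed from those who recruit. The protocol instead states a conditional switch: randomise, look at the groups, and force assignments if they differ. Followed as written, the assignment mechanism depends on what the accruing groups look like and on an undefined decision that they are unbalanced.

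The open label adds to this. Staff know the arms of patients they have treated. Someone who also knows the rule and the running imbalance can foresee a forced assignment from a new patient's age and surgical history.

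Foreknowledge could act through enrolment. Section 5 (2) allows exclusion of "Other patients who are judged to be inappropriate by the principal investigator and the investigator", and section 5 (4) removes patients who withdraw before the first dose. If patients are enrolled, deferred or excluded with the next assignment in mind, the arms can differ in prognosis for reasons no analysis can reliably undo. HADS, STAI, QOR and pain VAS are all patient-reported, so differences in baseline anxiety or sensitivity to pain could carry straight into them.

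**Working it through.** **The plan's own figure.** The only number needed from the protocol is the group size of about 40, in section 4 ⑤. That section gives "1-β was 80%, the significance level was 0.05", a 75% success rate with yokukansan, and "The clinically meaningful difference is defined as σ = 0.3". Reading 0.3 as a difference in rates (an assumption) implies 45% in the control group. The pooled two-sided formula for two proportions, with mean rate 0.60, gives

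n = [1.96 × √(2 × 0.60 × 0.40) + 0.842 × √(0.75 × 0.25 + 0.45 × 0.55)]² / 0.3² = (1.358 + 0.555)² / 0.09 = 40.7, so 41 per group.

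Power at 40 per group is 79.3%. The stated size reproduces on that reading. It enters below only through the standard error.

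**Possible size of selection bias (illustration).** Let f be the share of allocations that are foreseen and exploited, always in the same direction. Let η be the prognosis shift, so that patients enrolled under an expected intervention or control assignment differ by +η or −η SD. Neither value is in the protocol. I take η = 0.25 and vary f.

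- Bias in the arm difference = 2 × η × f.
- Standard error at 40 per group, in SD units = √(2/40) = 0.2236.
- Shift of the test statistic δ = bias / 0.2236.
- True error rate of a nominal two-sided 5% test = P(|Z + δ| > 1.96).

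| f | Bias (SD) | δ | True error rate |
|---|---|---|---|
| 10% | 0.05 | 0.224 | 0.0412 + 0.0145 = 5.6% |
| 25% | 0.125 | 0.559 | 0.0806 + 0.0059 = 8.6% |
| 50% | 0.25 | 1.118 | 0.1999 + 0.0010 = 20% |

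**How foreseeable forced assignments could be (illustration).** I simulated 80 patients with two assumed 50/50 binary factors, 600 runs per setting. Imbalance is the difference in arm counts, summed over the new patient's factor levels. When it reaches the trigger, the under-represented arm is assigned with the stated probability; otherwise assignment is 50/50. The observer knows all past assignments and guesses the under-represented arm.

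| Trigger | Forced with probability 1: correct guesses (share forced) | Probability 0.8: correct guesses |
|---|---|---|
| 1 | 86% (72%) | 74% |
| 2 | 70% (40%) | 66% |
| 4 | 60% (20%) | 59% |
| 6 | 57% (13%) | 55% |

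Pure randomisation gives about 50%. A forced assignment is certain under probability 1 and 80% certain under probability 0.8.

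**Does a 0.8 coin alone cure it?** No. Minimisation from the first patient corresponds to trigger 1 at 0.8, which gives 74% correct guesses. Forcing with probability 1 at triggers 2, 4 and 6 gives 70%, 60% and 57%. With four assumed factors the comparison is about 77% for 0.8 minimisation against about 80%, 68% and 62% for forcing at those triggers. The protection has to come from removing the trigger that depends on a look at the groups, and from concealed release.

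**The case against.** The text is short and reads as translated. It says an algorithm is created and calls the design forced random sampling. That may be an awkward rendering of minimisation or another rule-based adaptive method, which would be acceptable if pre-specified, run centrally and given a random element. This objection stands in part: it limits confidence and severity. It does not remove the point, because minimisation does not wait for a bias to be confirmed, and on either reading the factor list is open and the rule unstated. Allocation governs trial conduct and belongs in the protocol, so an unseen SAP does not answer it.

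A reader might infer more: that placement is deterministic, that an individual judges when to override, and that concealment is lost for the forced patients. The documents do not support this. Neither determinism nor a human decision-maker is stated. Open label reveals the arms of one's own patients, but in a two-hospital trial it does not show that staff see the other hospital's assignments or the running totals.

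The illustrated error rates are also open to challenge. They rest on assumed inputs and on every foreseen assignment being exploited in one direction.

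Finally, the unadjusted tests listed in section 4 ⑦ do not exclude adjustment, which is commonly left to an SAP. If the balancing factors predict outcome, those tests are conservative, which works against the inflation shown. Adjustment is therefore a secondary matter.

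**Conclusion.** The point holds as a poorly stated allocation rule, not merely as missing detail: the protocol provides for a switch from randomisation to forced assignment after inspection of the groups, on an open list of factors, in an open-label trial. The consequence is a risk of selection bias.

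The size of that risk cannot be computed from the document. The 5.6% to 20% range holds only for a ±0.25 SD prognosis shift with 10% to 50% of allocations foreseen and exploited at 40 per group. The 57% to 86% correct guesses under forcing hold only for the assumed triggers, factors and fully informed observer.

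This should be fixed, with moderate confidence, given the possible translation of a pre-specified adaptive method.

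**What to change.** Delete the conditional override in section 4 ④ [2] and state one allocation rule, fixed before the first patient. Either of two would serve:

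- computer-generated permuted blocks of varying size, concealed and stratified by hospital; or
- centrally run minimisation on a short closed list, for example hospital, age group and surgical history, with the assignment probability stated to be below 1.

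In either case, keep the running totals and the rule's parameters (block sizes or assignment probability) from recruiting staff, which means holding those values in a restricted document. Release each assignment only after consent, eligibility and baseline measures are recorded. Adjust the primary comparison for the allocation factors.

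If an adaptive method was already specified and in use, the amendment need only describe it in these terms.

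The cost is an amended paragraph and a small allocation program or service, with no extra patients. Balance will be slightly less exact than with forcing. Minimisation from the first patient can by itself be as guessable as rarely triggered forcing, or more so, so concealed release is essential to the change.

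### The interim stop and sample size recalculation rest on a response rate that is not an endpoint and that the planned Bayesian analysis does not estimate

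*Protocol*

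**What the plan says.** Protocol section 4 ⑤ (Sample size) plans an interim look: "an exploratory analysis will be performed when 20 cases in a group are reached". At that look, "the posterior probability of the response rate is calculated by an interim analysis, and the calculated posterior probability is monitored". Two consequences follow. The first is a stop: "If it is judged that the effect is not as good as that of untreated, the test should be discontinued". The second is a new sample size: "Recalculate the required number of cases based on the results of the interim analysis". The same paragraph justifies about 40 per group with 80% power, a significance level of 0.05, a 75% success rate under yokukansan and a meaningful difference of 0.3. Neither response nor success is defined.

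Section 4 ⑥ (Study endpoints) has "Primary endpoint: Salivary amylase level" and "Secondary endpoint: HADS STAI QOR Pain VAS".

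Section 4 ⑦ (Analysis method) has "For Bayesian statistics, the difference between two independent groups is estimated for the primary endpoint". The pre-analysis on the data of 20 subjects then supplies the prior for the final analysis. The trial is open label, and the analyst is someone other than the principal investigator.

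**The concern.** This is the only rule in the protocol that stops the trial on outcome data, and the final sample size depends on the same look. The rule is written for a proportion. The endpoints are a continuous level and scale scores, and the Bayesian model is for a difference in the continuous primary endpoint. An analyst who follows section 4 ⑦ at the interim obtains a posterior for the amylase difference, and section 4 ⑤ then asks for something else.

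To apply the rule as written, a responder definition must be supplied from outside the protocol, including which amylase measurement it uses (24 hours before, just before or 24 hours after surgery) and where the cut lies. Cutting a continuous measure into two discards information, and with 20 per group different reasonable cuts can give different answers from the same data. At stake are an unjustified stop, an unjustified continuation, and a recalculated sample size on a scale other than that of the final analysis.

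**Working it through.** **1. Which scale does section 4 ⑤ use?** The inputs there are 75% success, a difference of 0.3, power 80% and alpha 0.05. Two-sided testing is assumed. Reading 0.3 as a difference in proportions gives a control rate of 0.75 − 0.30 = 0.45 and a mean rate of 0.60.

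- Formula: n = [z₀.₉₇₅·√(2·p̄(1−p̄)) + z₀.₈₀·√(p₁(1−p₁) + p₂(1−p₂))]² / (p₁−p₂)²
- Numbers: [1.960·√0.480 + 0.842·√(0.1875 + 0.2475)]² / 0.09 = (1.358 + 0.555)² / 0.09 = 40.7, so **41 per group**.
- Other versions for two proportions: 38 with unpooled variance, 40.3 with the arcsine transformation, 39 one-sided with continuity correction.
- If 0.3 is instead a standardised mean difference: n = 2(1.960 + 0.842)² / 0.3² = 174.4, so **175 per group**.
- A mean difference of 0.3 in raw units would give 40 only with an SD of about 0.48, and the protocol states no amylase SD.

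The stated figure of about 40 is thus reproduced as 75% against 45%. Section 4 ⑤ is a response-rate design throughout, not just in one phrase.

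**2. The three parts of section 4 side by side.**

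| Part | Quantity | Type |
|---|---|---|
| ⑤ interim stop | response rate | proportion, undefined |
| ⑤ sample size | success rate 75%, difference 0.3 | proportion, undefined |
| ⑥ primary endpoint | salivary amylase level | continuous |
| ⑥ secondary endpoints | HADS, STAI, QOR, pain VAS | scale scores |
| ⑦ Bayesian analysis | group difference in the primary endpoint | continuous |

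Nothing in ⑥ or in the Bayesian part of ⑦ yields the quantity in the first row. Section 4 ⑦ also mentions Fisher's exact test for classified scales, but that defines no response either.

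**3. How much could the choice of cut-off matter?** The protocol gives no SD, cut-off or posterior limit, so all of the following are assumptions.

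- 20 per group, log amylase normal with SD 1, yokukansan mean lower by d.
- Response means a value below the cut-off. The five cut-offs are the control median and ±0.25 and ±0.5 SD around it.
- Beta(1,1) priors in each group. Stop if the posterior probability that yokukansan has the higher response rate is below the limit.
- d = 0.63 SD is the effect with 80% power at 40 per group: (1.960 + 0.842)·√(2/40) = 0.63.
- 20,000 simulated trials per effect.

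Share of trials in which at least two of the five cut-offs give opposite decisions:

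| Posterior limit | d = 0 | d = 0.3 | d = 0.63 |
|---|---|---|---|
| 0.20 | about 36% | about 14% | about 3% |
| 0.10 | about 22% | about 6% | about 1% |

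**4. Information lost by the cut.** In a separate run of 4,000 trials with limit 0.20, the chance of stopping at d = 0.3 is 3.8% when the rule is read on the mean difference, and 5.6% to 6.5% with cut-offs between −0.5 and +0.5 SD. At d = 0.5 it is 0.7% against 1.6% to 2.0%.

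**The case against.** Four points can be made against this.

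*The wording may be generic.* The opening of section 4 ⑤ describes Bayesian monitoring in general and is roughly translated, so section 4 ⑦ could be taken as giving this trial's actual quantity. That is possible but weak: the same paragraph assumes a success rate, and the stated 40 per group follows from two proportions.

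*A cut-off and a probability limit belong in an analysis plan.* This stands. Their absence alone would be no finding. But an analysis plan that defined response would still leave ⑤ monitoring something other than what ⑥ and ⑦ name, so one of them has to change.

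*A post hoc choice is not documented.* A reader might infer that someone will pick the cut-off at the interim with treatment known. The protocol does not say so. It is a risk in an open-label trial unless the definition is fixed beforehand. The separate analyst reduces that risk, although the protocol does not say the analyst is blinded.

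*The practical effect is modest where it matters most.* This also stands. A reader who simply compares the two raw response rates would find the decision depending on the cut-off in about half of trials with no effect. That amounts to a posterior limit near 0.5, whereas the protocol speaks of monitoring a posterior probability, so that figure should not be relied on. With no true effect, neither decision loses a useful treatment. At 0.63 SD with limit 0.20, a stop occurs in only about 0.8% to 1.0% of trials per cut-off. The design's own 75% against 45% corresponds to about 0.80 SD on a probit scale (0.674 + 0.126), where disagreement should be rarer still. The percentages also count any disagreement among five cut-offs, although a trial would use one.

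**Conclusion.** The inconsistency is real and lies within section 4 of the protocol. The stop and the sample size recalculation are tied to a proportion that is not an endpoint, while the planned Bayesian analysis estimates a difference in amylase. This conclusion rests on the text alone and needs no simulation.

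The size of the consequence is illustrative. Under the assumptions above, the decision depends on the cut-off in roughly 1% to 3% of trials at 0.63 SD, 6% to 14% at 0.3 SD and 22% to 36% with no effect, for limits of 0.10 and 0.20. Other cut-offs, limits or a non-normal log amylase would change these figures. They do not show that a clearly effective treatment would often be stopped. The point should be corrected because the rule cannot be applied from the protocol's own endpoints, and the remedy is available in an analysis already planned.

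**What to change.** In section 4 ⑤, replace the response rate in the interim rule with the quantity of section 4 ⑦: the posterior probability that amylase is lower with yokukansan than with control, at one named primary time point. Fix the limit for stopping before the interim data are opened. Naming the time point matters because amylase is measured three times; without it the new rule would leave a similar choice open.

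Base the sample size recalculation on the same amylase difference. Reconcile the 75% success rate and the 0.3 difference with that scale, stating the assumed amylase difference and SD. The separate analyst should release only the stop or continue decision and the recalculated number.

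Cost: no added patients, visits or measurements, and no new type of analysis. The study team gives up discretion at the interim. The sample size basis must be restated, which is more than a change of one phrase and may alter the figure of about 40 per group.
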